### **Patient-centered monitoring**

Randomization will also allocate patients into the following two groups:

- Standard monitoring arm: patients randomized in this arm will continue a standard 12-weekly routine immunological and safety blood monitoring, including CD4 cell count, lipids and glucose, renal and hepatic function tests, creatine kinase at their affiliated SHCS sites.
- Patient-centered monitoring arm: patients randomized in this arm will have immunological and safety blood analyses (CD4 cell count, lipids and glucose, renal and hepatic function tests, creatine kinase) performed at screening and at week 48. Additional safety blood tests will be performed in case of signs and symptoms as indicated by the physician. In addition, patients will have to choose at least one of three alternative options for the conduction of study visits, venipuncture and drugs delivery at weeks 6, 12 and 36, see section 8.1.1. Patients will also have the opportunity to change or give their opinion on the alternative option(s) chosen if they find it non convenient during the study. Changes will be possible at week 24; satisfaction will be assessed at week 12, 24, 36 and 48.

Importantly, all interventions or blood measurements potentially related to adherence (affecting the primary endpoint) will be identical between the study arms (see section 8.4).

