|-------------------------------------------------------------------------------------------------------------------------------------------------------------------------|----------------------------------------------------------------------------------------------------------------------------------------------------------------------------------------------------------------------|
| All visits at SHCS center                                                                                                                                               | Weeks 24 and 48 visits at SHCS center                                                                                                                                                                                |
| WHERE                                                                                                                                                            | Weeks 6, 12, 36 according to patient choice (see HOW below)                                                                                                                                                          |
|                                                                                                                                                                         |                                                                                                                                                                                                                      |
| Week 6:
- HIV-RNA measurement only
Weeks 12, 24, 36 and 48 visits:
- Complete blood analysis with HIV-RNA, CD4 count, full blood count, safety serum chemistry | Week 6, 12, 24, 36:
- HIV-RNA measurement only
Week 48:
- Complete blood analysis with HIV-RNA, CD4 count, full blood count, safety serum chemistry                                                         |
| WHAT                                                                                                                                                             |                                                                                                                                                                                                                      |

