### 9.2.4 Assessment of Safety Outcomes

#### 9.2.4.1 Adverse Events

At every study visit starting from the randomization in the trial, i.e. from the baseline visit, we will record adverse event information (i.e. type of event, date of onset, duration, final outcome, action to be taken, assessment of severity, relationship with study drug(s) and/or procedure). For the definition and procedures, we are referring to section 10. CNS side effects will be recorded using a standardized questionnaire at week 2 (by phone call) and week 6 among patients new to DTG drug and reported as adverse events as well. Assessment of adverse events will be standardized in the CRF.

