### **9.3.4. Week 6 ( $\pm$ 7 days)**

#### *Clinical assessments:*

- Adherence check by the study nurse/physician (face-to-face visit or by phone call);
- Recording/update of concomitant medications (face-to-face visit or by phone call);
- Adverse events recording (face-to-face visit or by phone call);

- CNS adverse event questionnaire for patients new to DTG (face-to-face visit or by phone call);
- Study drug distribution (DTG + FTC or standard cART) at study center, chosen pharmacy or by mail depending of study arm and option(s) chosen by the patient.

*Laboratory assessments (at SHCS center or peripheral laboratory):*

- HIV-1 RNA in plasma;
- Plasma sample storage;
- Dolutegravir and emtricitabine plasma concentration if HIV-1 RNA measurement  $\geq 100$  copies/ml in plasma;
- Genotypic resistance test if 2 consecutive HIV-1 RNA measurements  $\geq 100$  copies/ml in plasma;
- Pharmacogenetic analyses if 2 consecutive HIV-1 RNA measurements  $\geq 100$  copies/ml in plasma only for patients included in the SHCS and who have signed a consent form for genetic studies;
- CK, ASAT/ALAT, gamma-GT and alkaline phosphatases if patient new to DTG drug;
- Glucose and creatinine if patient under DTG and metformine.

For patients randomised in the patient-centered monitoring arm, study drug distribution and laboratory assessments can be done before clinical assessments but within the time window of the visit.

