### **9.3.5. Weeks 12 and 36 ( $\pm 7$ days)**

*Clinical assessments:*

- Adherence check by the study nurse/physician (face-to-face visit or by phone call);
- Recording/update of concomitant medications (face-to-face visit or by phone call);
- Adverse events recording (face-to-face visit or by phone call);
- Questionnaires completion: visual analog scale, PROQOL-HIV, (face-to-face visit or by phone call);
- Study drug distribution (DTG + FTC or standard cART) at study center, chosen pharmacy or by mail depending of study arm and option(s) chosen by the patient;
- Patient's monitoring satisfaction.

*Laboratory assessments (at SHCS center or peripheral laboratory):*

- HIV-1 RNA in plasma
- Plasma sample storage;
- Dolutegravir and emtricitabine plasma concentration if HIV-1 RNA measurement  $\geq 100$  copies/ml in plasma;
- Genotypic resistance test if 2 consecutive HIV-1 RNA measurements  $\geq 100$  copies/ml in plasma;
- Pharmacogenetic analyses if 2 consecutive HIV-1 RNA measurements  $\geq 100$  copies/ml in plasma only for patients included in the SHCS and who have signed a consent form for genetic studies;
- CD4 count, full blood count, safety serum chemistry (CK, creatinine, ASAT/ALAT, gamma-GT, alkaline phosphatases, glucose and lipids) if patient randomised in standard monitoring arm;
- Glucose, and creatinine if patient under DTG and metformine and patient-centered monitoring arm.

For patients randomised in the patient-centered monitoring arm, study drug distribution and laboratory assessments can be done before clinical assessments but within the time window of the visit.

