#### 10.1.1. Definition and assessment of (Serious) Adverse Events and other safety related events

An **Adverse Event (AE)** is any untoward medical occurrence in a patient or a clinical investigation participant administered a pharmaceutical product and which does not necessarily have a causal relationship with the study procedure. An AE can therefore be any unfavourable and unintended sign (including an abnormal laboratory finding), symptom, or disease temporally associated with the use of a medicinal (investigational) product, whether or not related to the medicinal (investigational) product.

Adverse Events that need to be reported in this study are listed in the Adverse Event list (see Appendix 6). This list will be used starting from the baseline visit to confirming the absence or presence of any listed adverse event. Spontaneous, non-serious Adverse Events that are not listed in the Appendix 6 list will be collected in the patient's medical file according to local usual practice but will not be reported into the study-related document. Laboratory abnormalities listed in the Adverse Event list, will be reported as Adverse Events if they are at least a grade 3 and if they appear after randomization in the study (i.e. starting from the baseline visit). In case of laboratory abnormality already present before the randomisation, this will be considered as an adverse event only in case of worsening.

A **Serious Adverse Event (SAE)** is classified as any untoward medical occurrence that:

- results in death,
- is life-threatening,
- requires in-patient hospitalization or prolongation of existing hospitalisation,
- results in persistent or significant disability/incapacity,
- results in a congenital anomaly/birth defect, or
- is an important medical events that may not be immediately life-threatening or result in death, or require hospitalisation, but may jeopardise the patient or may require intervention to prevent one of the other outcomes listed above should also usually be considered serious. Examples of such events are intensive treatment in an emergency room or at home for allergic bronchospasm, blood dyscrasias or convulsions that do not result in hospitalisation, or development of drug dependency or drug abuse.

SAEs should be followed until resolution or stabilisation. See details in section 10.1.3.

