#### 11.4.2 Primary analysis

As a first step in this factorial trial, we will test for an interaction between the type of drug treatment and the monitoring type in order to assess if treatment effect is different depending on the type of monitoring. If the test is non-significant we will combine the two types of monitoring for the drug therapy comparison and the two drug therapies for the monitoring comparison. Otherwise, the trial will be analysed as a four-arm trial with a hierarchical testing approach.

For the primary comparison of the primary outcome between the two treatment arms, we will obtain the proportion of patients with viral suppression for 48 weeks in each arm, and compute a Mantel-Haenszel risk difference (DTG+FTC - cART) stratified for the monitoring type with a two-sided 95% confidence interval (107). If the lower confidence limit is higher than -12% we will conclude non-inferiority. If the lower confidence limit is below -12% we will conclude that DTG + FTC is potentially inferior to cART.

For the secondary comparison of the primary outcome between the two monitoring arms, we will calculate a Mantel-Haenszel test statistics and Mantel-Haenszel risk difference (DTG+FTC - cART) stratified for the type of treatment.

Secondary categorical outcomes (proportions of virological suppression <50 copies/mL both as a standard proportion and as FDA snapshot, of loss of future treatment options, of adverse events, of serious adverse events, of CSN adverse events, of CNS symptoms) between the DTG+FTC and cART groups, and between the patient-centered and standard monitoring groups will also be analysed using the Mantel-Haenszel test statistics and Mantel-Haenszel risk difference (DTG+FTC - cART) stratified for the type of monitoring and type of treatment, respectively.

For continuous outcome variables (CD4 count, HIV-DNA level, total cholesterol, high-density lipoproteine, triglycérides, low density lipoprotein-cholesterol, glucose, Framingham-calculated cardiovascular risk, glomerular function rate, weight, health-related quality of life, treatment satisfaction), we will compare the mean values at 48 months between the DTG+FTC and cART treatment groups and between the patient-centered and standard monitoring groups using linear regression adjusted for the type of monitoring and type of treatment, respectively.

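### Adverse event proportions are compared between arms in which events are looked for unequally, and the CNS-symptom comparison with cART has no comparator data

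*Protocol*

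**What the plan says.** **What counts as an AE.** Under section 10.1.1, laboratory abnormalities on the Appendix 6 list "will be reported as Adverse Events if they are at least a grade 3 and if they appear after randomization in the study". An abnormality already present before randomisation counts only if it worsens.

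**Monitoring arms.** Table 1 in section 8.1.1 gives complete blood analyses under standard monitoring at "Weeks 12, 24, 36 and 48 visits". Section 9.3.5 (weeks 12 and 36) orders "CD4 count, full blood count, safety serum chemistry (CK, creatinine, ASAT/ALAT, gamma-GT, alkaline phosphatases, glucose and lipids) if patient randomised in standard monitoring arm", and section 9.3.6 repeats this for week 24. In the patient-centered arm, section 6.1 has the immunological and safety analyses "performed at screening and at week 48. Additional safety blood tests will be performed in case of signs and symptoms as indicated by the physician". The footnotes to section 9.1 add two exceptions that apply in either monitoring arm: week-6 CK and hepatic tests for patients new to DTG, and glucose and creatinine at weeks 6 to 36 for diabetic patients on metformin and DTG.

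**Drug arms.** Section 9.2.4.1 records CNS side effects by standardised questionnaire "at week 2 (by phone call) and week 6 among patients new to DTG drug and reported as adverse events as well". Section 3.7 places this questionnaire in the dual-therapy arm. Section 9.3.4 adds at week 6 "CK, ASAT/ALAT, gamma-GT and alkaline phosphatases if patient new to DTG drug".

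**Comparisons.** Section 11.4.2 lists AEs, serious AEs, CNS AEs and CNS symptoms among the categorical outcomes. It compares them between DTG+FTC and cART, and the differences "between the patient-centered and standard monitoring groups will also be analysed using the Mantel-Haenszel test statistics". Section 11.4.5 also compares drug-related events between the treatment arms across study time-points.

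**The concern.** In each comparison, one arm has more opportunities for an event to be found. A grade 3 laboratory abnormality that appears at week 12 and resolves by week 48 is an AE under standard monitoring. Under patient-centered monitoring it goes unrecorded unless symptoms prompt a test or an exception applies. The randomised factor therefore partly determines how often its own safety outcome is measured. The error flatters the strategy that section 3.1 wants to show does not jeopardise safety.

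In the drug comparison the error runs the other way, because the additional contact, questionnaire and tests fall on DTG+FTC patients new to DTG.

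The safeguard in section 6.1, that procedures are identical between arms, covers only those related to adherence. Stratifying by the other factor, as section 11.4.2 does, cannot correct unequal ascertainment within the factor being compared.

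**Working it through.** **1. Scheduled assessments after randomisation**

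| Comparison | More closely observed arm | Other arm |
|---|---|---|
| Monitoring: full safety panels | Standard: 4 (weeks 12, 24, 36, 48) | Patient-centered: 1 (week 48), plus symptom-driven tests and the two exceptions |
| Drug: CNS questionnaires | DTG+FTC, new to DTG: 2 (weeks 2 and 6) | Continuing cART: 0 |
| Drug: week-6 CK and liver tests | DTG+FTC, new to DTG: 1 | Continuing cART: 0 |

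All patients have an AE check at every scheduled visit from day 0 (section 9.1). The drug-arm differences come on top of that check.

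**2. Laboratory illustration with no true difference**

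The protocol gives no rates, so these are assumptions: p is the chance of a new listed grade ≥3 abnormality per panel interval, and s is the share that persists to week 48. Symptom-driven tests and the exceptions are left out.

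- Standard monitoring: 1 − (1 − p)^4
- Patient-centered monitoring: 1 − (1 − p)(1 − ps)^3

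At p = 1% the standard arm shows 1 − 0.99^4 = 3.9%. With s = 0.5 the patient-centered arm shows 1 − 0.99 × 0.995^3 = 2.5%. The last column is the rejection rate of a two-sided 5% Pearson test at 92 per group (section 11.2), by exact binomial enumeration.

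| p | s | Standard | Patient-centered | Difference (points) | Rejection rate |
|---|---|---|---|---|---|
| 1% | 0 | 3.9% | 1.0% | 2.9 | 22% |
| 1% | 0.5 | 3.9% | 2.5% | 1.5 | 8% |
| 1% | 1 | 3.9% | 3.9% | 0 | 4% |
| 2% | 0 | 7.8% | 2.0% | 5.8 | 43% |
| 2% | 0.5 | 7.8% | 4.9% | 2.9 | 11% |
| 2% | 1 | 7.8% | 7.8% | 0 | 5% |

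Among 92 patients per group, 2.9 points is about 2.7 patients and 5.8 points about 5.3.

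**3. Drug comparison**

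Let b be the proportion with an AE recorded through the common checks, f the share of DTG+FTC patients new to DTG, and e the extra proportion elicited in those patients. With no true difference, DTG+FTC shows 1 − (1 − b)(1 − fe) and cART shows b. The protocol supplies none of the three. With b set at 5%:

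- f = 25%, e = 5%: 1 − 0.95 × 0.9875 = 6.19% vs 5%
- f = 50%, e = 10%: 1 − 0.95 × 0.95 = 9.75% vs 5%
- f = 75%, e = 20%: 1 − 0.95 × 0.85 = 19.25% vs 5%

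The artefact runs from about 1 to about 14 points depending on unknown inputs. This shows the direction and the dependence on f and e. It is not an estimate.

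**4. CNS symptoms**

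Section 5.2 item 13 defines this outcome only in patients new to DTG, at 2 and 6 weeks after starting it. Sections 9.3.3 and 9.3.4 schedule the questionnaire only for them. Section 11.4.2 nevertheless lists CNS symptoms among the outcomes to be compared between DTG+FTC and cART. Patients who simply continue cART have no scheduled data for that test.

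**The case against.** A reader might infer that cART patients are never asked about CNS events, or that their events surface only by spontaneous report. The documents do not support this. Section 10.1.1 has the Appendix 6 list worked through from baseline to confirm whether each listed event is present or absent, and section 9.2.4.1 says assessment is standardised in the CRF. Whether the list covers CNS symptoms cannot be seen here. What cART patients lack is the additional contact, the questionnaire and the week-6 tests. Nor is the whole DTG+FTC arm affected: section 7.1 admits patients on two NRTIs plus an integrase inhibitor and does not bar prior DTG.

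A reader might also take four panels versus one at face value as the size of the laboratory bias. That is the extreme case in which nothing persists to week 48. Symptom-driven tests, the two exceptions and the grade 3 threshold reduce it further.

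The stakes are also limited. Section 11.1 has no safety hypothesis for monitoring, section 4.1 aims to describe safety, and section 11.2 concedes low power for AEs. CD4, lipids, glucose, renal function and weight at week 48 are measured alike in all arms, and serious AEs defined by death or hospitalisation are little affected. Fewer panels are a legitimate part of the intervention, and an analysis plan not shown may add sensitivity analyses.

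All of this limits the size and consequence of the problem. It does not remove the mechanism, because the AE definition, the visit schedule and the between-arm comparisons are all fixed in the protocol.

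**Conclusion.** The point holds as a directional bias in secondary and safety comparisons.

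- **Monitoring:** the comparison favours patient-centered monitoring to the extent that abnormalities are transient. Under the assumed 1-2% per panel, the artefact is 2.9 to 5.8 points if all resolve, 1.5 to 2.9 points if half persist, and zero if all persist.
- **Drug:** the comparison tends to make DTG+FTC look worse. The amount cannot be fixed from the protocol, because it depends on the share new to DTG and on the unseen Appendix 6 list.
- **CNS symptoms:** the comparison with cART cannot be made as written. This conclusion needs no assumed rate.

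Each imbalance belongs to its own comparison. Monitoring is randomised across both drug arms and stratified for, so the panel schedule does not bias the drug comparison; likewise, the questionnaire does not bias the monitoring comparison. The reduced testing is not itself at fault. The fault lies in using an AE proportion that depends on the amount of testing as the comparative safety outcome.

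**What to change.** Amend sections 11.4.2 and 11.4.5 and leave all clinical monitoring unchanged.

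- **Monitoring comparison:** compare clinical AEs plus laboratory abnormalities obtained by grading the week-48 values against the pre-randomisation baseline in both arms. Report laboratory AEs from weeks 6 to 36 descriptively by arm. Do not select laboratory AEs by the visit at which they were first recorded. An abnormality first recorded at week 12 and still present at week 48 is not a new record at week 48, so the standard arm would be undercounted. At p = 1% and s = 0.5, a visit filter would leave about 1.0% in the standard arm (onsets in the last interval only) against 2.5% in the patient-centered arm, which reverses the bias. Grading the week-48 values gives 2.5% in both.
- **Drug comparison:** keep all AEs in the main table, so that early CNS events, a risk the protocol flags itself, stay visible. Add a sensitivity analysis that excludes AEs first recorded at the week-2 call or identified only by the week-6 questionnaire or the week-6 CK and liver tests.
- **CNS symptoms:** report them descriptively in patients new to DTG and remove them from the DTG+FTC versus cART tests.

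The cost is a field on AE records for the source of detection, a grading of week-48 values, and slightly fewer laboratory events in the monitoring comparison. The week-6 AE check and questionnaire take place at the same visit, so the source has to be recorded at the time.

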#### Assessment of Causality of (Serious) Adverse Events and other safety related events

The Study Investigator makes a causality assessment of the event to the study drug and study procedure using the categories based on the ICH E2A guidelines:

| Relationship | Description                                                                                                                  |
|--------------|------------------------------------------------------------------------------------------------------------------------------|
| Certain      | Temporal relationship +
Improvement after dechallenge +
Recurrence after rechallenge
(or other proof of drug cause) |
| Probable     | Temporal relationship + Improvement after dechallenge
No other cause evident                                              |

|                |                                                                   |
|----------------|-------------------------------------------------------------------|
| Possible       | Temporal relationship
Other cause possible                     |
| Unlikely       | Any assessable reaction that does not fulfil the above conditions |
| Excluded       | Causal relationship can be ruled out                              |
| Not assessable | Not assessable                                                    |

In case of an Adverse Event at least possibly related to the study drug, DTF and FTC plasma concentration measurement can be performed at treating physician discretion as standard of care.

### **Unexpected Adverse Drug Reaction**

An unexpected adverse drug reaction is an adverse reaction, the nature or severity of which is not consistent with the applicable product information (e.g. Investigator's Brochure for drugs that are not yet approved and Product Information for approved drugs, respectively).

